### **8.5. Safety Analysis**

Safety parameters will be listed and summarised using descriptive statistics. No formal statistical analysis of safety data is planned. Each AE will be coded using the Medical Dictionary for Regulatory Activities. The number of subjects with abnormalities in clinical laboratory measurements and the number of subjects with vital signs measurements or ECG parameters meeting criteria of potential clinical concern from baseline through the Follow-up visit will be summarised.

The vital signs criteria of potential clinical concern are as follows:

- supine pulse rate <40 bpm or >120 bpm
- standing pulse rate <40 bpm or >140 bpm
- systolic blood pressure  $\geq 30$  mmHg change from baseline in same posture or <90 mmHg
- diastolic blood pressure  $\geq 20$  mmHg change from baseline in same posture or <50 mmHg.

The ECG criteria of potential clinical concern are as follows:

- PR interval  $\geq 300$  msec,  $\geq 25\%$  increase when baseline is >200 msec, or  $\geq 50\%$  increase when baseline is  $\leq 200$  msec
- QRS interval  $\geq 140$  msec or  $\geq 50\%$  increase from baseline
- QTcF  $\geq 450$  msec to <480 msec,  $\geq 480$  msec to <500 msec, or  $\geq 500$  msec.

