### **3.7. Dose Escalation Stopping Criteria**

The dose level for this study will not exceed 600 mg. In addition, dosing will be stopped and dose progression will be halted until safety information can be reviewed in the event that:

- One or more subjects experience a serious AE (SAE) that is considered to be related to IMP or 2 or more subjects experience severe AEs that are considered to be related to IMP
- There is evidence of clinically significant increases in liver function tests (aspartate aminotransferase, alanine aminotransferase, alkaline phosphatase, bilirubin, and/or gamma-glutamyl transferase), defined as 3 times the upper limit of normal in 3 or more subjects in a cohort compared to Day -1 measurements (confirmed with repeat testing)
- QTcF increases >60 msec compared to baseline and/or absolute QTcF values >500 msec (confirmed by single repeat measurement) in 2 or more subjects in a cohort

- Severe diarrhoea, defined as 7 or more episodes, rated as  $\geq 5$  on the Bristol Stool Chart, in 1 day for 2 consecutive days in 2 or more subjects in a cohort
- The exposure for any subject in the planned dosing cohort is predicted to exceed an  $AUC_{0-24}$  of 51,800 ng.h/mL for derived total KL1333 (as the sum of parent KL1333, de-conjugated glucuronidated KL1333 metabolites, and sulphated KL1333 metabolites). For Part D,  $AUC_{0-24}$  will be determined as  $AUC_{0-\tau} \times 2$  for BID and  $AUC_{0-\tau} \times 3$  for TID regimens.

If, following an internal safety review, the Sponsor deems it appropriate to restart the study, this can be done following approval of a substantial protocol amendment.

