12. Use or intend to use any medications/products known to alter drug absorption, metabolism, or elimination processes, including St. John's wort, within 30 days prior to the first dose, unless deemed acceptable by the Investigator.
13. Receipt of blood products within 2 months prior to Screening.
14. Donation of blood from 3 months prior to Screening, plasma from 2 weeks prior to Screening, or platelets from 6 weeks prior to Screening.
15. Poor peripheral venous access that precludes collection of blood samples.
16. Have previously completed or withdrawn from this study and have previously received the IMP. Subjects who received IMP in Part A will not be allowed to participate in Part B or Part D.
17. Member of the study personnel or their immediate families, or is a subordinate or immediate family member of a subordinate to any of the study personnel.
18. Has a disease (except for mitochondrial disease in the patients in Part C) or takes medication that could interfere with the conduct or interpretation of the study, in the opinion of the Investigator.
19. Should not participate in this study or is unlikely to comply with the protocol, in the opinion of the Investigator.

Additional exclusion criteria for healthy subjects:

20. Dietary restriction that would prevent the subject from consuming the high-fat breakfast (Table 5).
21. Significant history or clinical manifestation of any metabolic, allergic, dermatological, hepatic, renal, haematological, pulmonary, cardiovascular, gastrointestinal, neurological, respiratory, endocrine, or psychiatric disorder, as determined by the Investigator.
22. Any of the following vital signs abnormalities. A single repeat is allowed for eligibility based on the Investigator's judgment:
  - Systolic blood pressure <90 mmHg or >160 mmHg
  - Diastolic blood pressure <50 mmHg or >90 mmHg
  - Pulse rate <40 bpm or >100 bpm.
23. Any of the following ECG abnormalities. A single repeat testing is allowed for eligibility based on the Investigator's judgment:
  - Abnormal ECG that is clinically significant, as determined by the Investigator
  - PR interval >250 msec
  - QRS interval >130 msec
  - QTcF >450 msec (for males) or >470 msec (for females).
24. Use or intend to use any prescription medications/products within 14 days prior to the first dose, unless deemed acceptable by the Investigator.

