25. Use or intend to use slow-release medications/products considered to still be active within 14 days prior to the first dose, unless deemed acceptable by the Investigator.
26. Use or intend to use any nonprescription medications/products including vitamins, minerals, and phytotherapeutic/herbal/plant-derived preparations within 7 days prior to the first dose, unless deemed acceptable by the Investigator.
27. Use of tobacco- or nicotine-containing products within 3 months prior to Screening.

Additional exclusion criteria for patients with mitochondrial disease:

28. Any of the following ECG abnormalities. Triplicate repeat testing is allowed for eligibility based on the Investigator's judgment:
  - Abnormal ECG that is clinically significant, as determined by the Investigator
  - QTcF >500 msec.
29. Patient requires antiepileptic medication that might have an effect on CYP or glucuronyl transferase enzymes (eg, phenytoin, carbamazepine, and valproic acid).
30. Patient requires medication that is metabolized by the following CYPs and the Investigator and Medical Monitor, in consultation with the Sponsor, consider there to be a potential risk for a clinically significant drug interaction:
  - CYP1A2 (eg, clozapine, fluvoxamine, haloperidol, imipramine, nabumetone, naproxen, olanzapine, theophylline, tizanidine, and zolmitriptan)
  - CYP2B (eg, temazepam, diazepam, selegiline, mephobarbital, and mexiletine)
  - CYP3A4 (eg, clarithromycin, erythromycin, quinidine, alprazolam, diazepam→3OH, midazolam, triazolam, cyclosporine, tacrolimus [FK506], sirolimus, astemizole, chlorpheniramine, diltiazem, verapamil, atorvastatin, lovastatin, simvastatin, sildenafil, tadalafil, vardenafil, quinine, alprazolam, ketoconazole, itraconazole, and zolpidem).
31. Use of idebenone or medications (prescription or nonprescription) that have effects on metabolism or unknown binding sites (eg, vitamin E, co-enzyme 10, arginine) within 7 days or 5 half-lives, whichever is longer, prior to the first dose.
32. Use of prescription drugs within 14 days prior to dosing, with the exception of hormone replacement therapy; oral, implantable, transdermal, injectable, or intrauterine hormonal contraceptives; and established therapy for mitochondrial disease and the treatment of associated disorders that has been stable for at least 7 days prior to the first dose, as approved by the Medical Monitor and Investigator, in consultation with the Sponsor.

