| C-reactive protein, erythrocyte sedimentation rate, and faecal calprotectin k |                                  | X         |                                         |                |          |                |                   |                |          | X g |           |    |                       |
| Blood pressure, pulse rate, and body temperature l                            | X                                | X         | Predose and 2, 4, and 10 hours postdose | X g |          | X g |                   | X g |          | X g | X         | X  | X                     |
| Safety 12-lead ECG m                                                          | X                                | X         | 2 hours postdose                        | X g |          | X g |                   | X g |          | X g | X         | X  | X                     |
| Complete physical examination                                                            | X n                   |           |                                         |                |          |                |                   |                |          |                |           | X  | X                     |
| Symptom-directed physical examination                                                    |                                  |           | X g                          | X g |          | X g |                   | X g |          | X g | X         |    |                       |
| Exit interview                                                                           |                                  |           |                                         |                |          |                |                   |                |          |                | X         | X  |                       |

Abbreviations: ECG = electrocardiogram; ET = early termination; HbA1c = glycated haemoglobin.

a Interim medical history.

b In all females. Performed in serum at Screening and in urine at all other times. A positive urine pregnancy test will be confirmed with a serum pregnancy test.

c In postmenopausal females.

d Height measured at Screening only.

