| Safety 12-lead ECG                                                                       | X                             | X j | Day 1: 2 hours post first dose
Days 2 to 9: Prior to first dose
Day 10: Predose
Days 11 and 12                                                                                              |                   | X                    | X                     |
| Complete physical examination                                                            | X k                |                |                                                                                                                                                                                                      |                   | X                    | X                     |
| Symptom-directed physical examination                                                    |                               |                | Days 1 to 9: Prior to first dose
Day 10: Predose
Days 11 and 12                                                                                                                                |                   |                      |                       |

Abbreviations: BID = twice daily; ECG = electrocardiogram; TID = 3 times daily.

a Interim medical history.

b In all females. Performed in serum at Screening and in urine at all other times. A positive urine pregnancy test will be confirmed with a serum pregnancy test.

c In postmenopausal females.

d Height measured at Screening only.

e Biomarkers includes nicotinamide adenine dinucleotide (oxidized form)/nicotinamide adenine dinucleotide (reduced form), pyruvate, lactate, and other biomarkers.

f Blood for metabolomics will include a whole blood sample and a serum sample at each timepoint.

g Clinical chemistry, haematology, and urinalysis. Subjects will be fasted at least 8 hours.

h Up to 3 additional symptom-directed evaluations may be performed based on the Investigator's judgment.

i Supine and standing blood pressure and pulse rate. Blood pressure and pulse rate prior to the first dose on Day 1 will be measured in triplicate.

j Measured in triplicate.

k Performed between the Screening visit and assessments prior to the first dose.

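### Section 8.5 counts safety-ECG QTcF only in absolute bands from baseline, so unchanged long QTcF is counted and rises of more than 30 msec that end below 450 msec are not

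*Protocol*

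**What the plan says.** Twelve-lead ECG parameters are a primary safety endpoint (Section 2.2.1). Section 8.5 plans a descriptive analysis and adds a count of subjects with "ECG parameters meeting criteria of potential clinical concern from baseline through the Follow-up visit will be summarised". The QTcF criteria begin with "QTcF $\geq 450$ msec to <480 msec" and continue with 480 to <500 msec and 500 msec or more. All three are absolute values. The blood pressure criteria in the same section include a "mmHg change from baseline in same posture", and PR and QRS each include a percentage increase from baseline.

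Entry limits are in Section 4.2. Healthy subjects are excluded for "QTcF >450 msec (for males) or >470 msec (for females"; patients with mitochondrial disease only for "QTcF >500 msec".

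The rules for running the study do use change. The criterion in Section 3.7 is "QTcF increases >60 msec compared to baseline and/or absolute QTcF values >500 msec" in 2 or more subjects in a cohort. Section 4.4 has the same thresholds for withdrawal of an individual in Part C, and Section 7.3.5.1 repeats the ECG when the change from Day -1 exceeds 60 msec.

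QTcF change categories (>30 to ≤60 and >60 msec) appear only in Section 8.5.1.5, which covers the continuous ECGs of Parts A and B. Section 7.3.5.2 says those recordings are stored unanalysed and that any later analysis falls outside this study's report.

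**The concern.** A count of subjects of concern should separate what the drug may have done from what the subject brought to the study. The rule as written does not do this for QTcF. It counts from baseline in a population whose entry limits overlap the bands, so a long but unchanged QTcF is reported as a finding. It also has no category for a substantial rise from a normal baseline that stays under 450 msec. The protocol itself treats a change of more than 60 msec as important enough to repeat an ECG, halt dosing or withdraw a Part C patient, yet the reported count leaves change out. Because the continuous-ECG analysis is set aside, the safety ECG is the only ECG result this study commits to report.

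**Working it through.** Section 8.1 says no formal sample-size assessment was made, and no power or error rate lies behind this point, so there is no figure of the plan to reproduce. The check applies the stated rules to example values.

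**1. Overlap of entry limits with the bands.** The lowest band starts at 450 msec. Eligible baselines already inside a band are 450 to 470 msec for healthy women (limit 470) and 450 to 500 msec for patients (limit 500). For healthy men only the single value 450 overlaps.

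**2. Rises that reach no band.** A rise above d msec can end below 450 msec whenever the baseline is below 450 − d. For d = 30 that is any baseline below 420 msec; for d = 60, any baseline below 390 msec.

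**3. Examples (msec).**

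| Baseline → postdose | Change | Section 8.5 band | Band by the Section 8.5.1.5 change cut-points |
|---|---|---|---|
| 385 → 445 | +60 | none | >30 to ≤60 |
| 388 → 449 | +61 | none | >60 |
| 400 → 445 | +45 | none | >30 to ≤60 |
| 410 → 445 | +35 | none | >30 to ≤60 |
| 460 → 460 | 0 | 450 to <480 | none |
| 485 → 485 | 0 | 480 to <500 | none |
| 495 → 495 | 0 | 480 to <500 | none |

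The first four subjects changed and are not counted. The last three did not change and are counted. The 460 could be a healthy woman or a patient; 485 and 495 could only be patients.

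**4. Weight of one subject.** Part C has 6 active and 2 placebo patients. One patient with a stable long QTcF contributes 1/6 = 17% in the active arm or 1/2 = 50% in the placebo arm.

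**5. How often a real rise would be missed by the bands (illustration).** The documents give no QTcF distribution. Assume normal values with baseline mean m of 395 to 415 msec, SD s of 15 to 20 msec, and a uniform rise of 40 msec. Then P(QTcF ≥ 450) = 1 − Φ((450 − m − 40)/s).
- m = 395, s = 15: 1 − Φ(15/15) = 0.159.
- m = 415, s = 15: 1 − Φ(−5/15) = 0.631.

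The other combinations fall between these. So about 16% to 63% of such subjects would reach a band, and 37% to 84% would not.

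**6. When the safety ECGs are taken (Appendix 5).** Part B: 2 hours postdose on Day 1, predose on Days 2 to 10, then Days 11 and 12. Part C: 2 hours postdose on Day 1, predose on Days 2, 4, 8 and 10, then Day 11. Part D: "Day 1: 2 hours post first dose", before the first dose on Days 2 to 9, predose on Day 10, then Days 11 and 12. After Day 1, no scheduled safety ECG on a dosing day follows that day's first dose.

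**The case against.** The best defence is that little is truly lost. A rise above 60 msec triggers a repeat ECG, counts toward the Section 3.7 criterion and, if confirmed in Part C, leads to withdrawal. All safety data are listed, and the Investigator assesses every ECG. With 6 active and 2 placebo subjects per cohort, individual listings say more than band counts. Most of this stands: a reader might infer that a rise from 380 to 445 msec would go unseen, and the documents do not support that. What remains is that such a rise is not counted, and that rises of more than 30 and up to 60 msec ending below 450 msec meet neither a reporting category nor a QTcF conduct threshold.

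Second, the SAP may add change bands and shift tables, and counting from baseline may be meant as counting after baseline. The SAP is not at hand, so this is possible. But Section 8.5 does fix the QTcF list, and fixes it differently from its neighbours. Even a strictly postdose count would include an unchanged 460 or 495 msec.

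Third, Section 8.5.1 describes a full analysis of the continuous ECGs, including change bands. Section 7.3.5.2 places that outside this report, and it would in any case cover Parts A and B only.

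A stronger reading is also tempting: that predose ECGs after Day 1 mean a QTcF effect would be missed, so the Day 10 ECG should be moved. The documents do not support this. Parts B to D each have an ECG 2 hours after the first dose, near the median Tmax of 1 to 2 hours in Table 3. Under linear accumulation, the lower the trough is relative to the peak, the closer that Day 1 level already is to the steady-state one; if the trough is high, the predose ECGs themselves see a substantial share of the peak. Moving the Day 10 record would also give up a check before the last dose.

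**Conclusion.** The point holds for the reporting criteria. As written, Section 8.5 counts QTcF values that were long at entry and did not change, and has no category for rises of more than 30 msec that end below 450 msec, which is possible for any baseline below 420 msec. This follows from the protocol's own limits and needs no assumption; only the 37% to 84% in the illustration rests on an assumed QTcF distribution. It is a defect of reporting, not of monitoring: rises above 60 msec remain visible through the conduct rules and listings. The timing of the safety ECGs is a limitation to state, namely that the reported QTcF results do not describe steady-state peak concentrations. It is not evidence that an effect would be missed.

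**What to change.** In Section 8.5, and in the SAP tables:

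- Add QTcF increase from baseline of >30 to ≤60 msec and of >60 msec, the cut-points already in Section 8.5.1.5.
- Count a subject in an absolute band only if a postdose value falls in a category worse than that subject's baseline category.
- Give a shift table of baseline category by worst postdose category, by treatment.
- State as a limitation that after Day 1 the scheduled safety ECGs on dosing days in Parts B to D are predose, so these results do not describe QTcF at steady-state peak concentration.

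The Day -1 ECGs needed for the baseline are already taken in triplicate in every part. The cost is table programming and a short text change; no visit, sample or ECG is added or moved.

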### **8.5.1. Cardiodynamic Electrocardiogram Evaluation**

This section addresses the cardiodynamic ECG assessment from continuous 12-lead ECG recordings (Holters) for Parts A and B only. The primary analysis will be based on concentration-QTc modelling of the relationship between KL1333 and  $\Delta$ QTcF with the intent to exclude an effect >10 msec at clinically relevant KL1333 plasma concentrations. In addition, the effect of KL1333 on the  $\Delta\Delta$ QTcF will be evaluated at each postdose timepoint ('by-timepoint' analysis) using the Intersection Union Test. An analysis of categorical outliers will be performed for changes in HR; PR, QRS, and QTcF intervals; T-wave morphology; and U-wave presence.

#### **8.5.1.1. General Methodology**

All statistical analyses will be performed using the statistical software SAS for Windows Version 9.4 or newer (SAS Institute, Inc., Cary, NC, USA). In all calculations, zero will be substituted for concentrations below the quantification limit of the assay. Data collected from all randomised subjects will be presented in data listings. Both absolute values and change-from-baseline values for each subject will be given where applicable. All continuous data will be listed with the same precision as will be presented in the database. Data listings will be sorted by treatment, subject number, and timepoint. Missing values will be represented by an empty cell and no imputation will be made.

Continuous data will be summarised using descriptive statistics including number of subjects, mean, median, standard deviation (SD), standard error (SE), 90% confidence interval (CI), minimum, and maximum by treatment and timepoint. Mean and median values will be rounded to the nearest tenth, or to the first nonzero decimal; SD, SE, and CI will be rounded to the nearest hundredth, or to 1 digit more than the nearest nonzero digit. For the concentration-QTc analysis, 3 significant figures will be kept for the effect estimates. *P*-values will be reported with 4 significant digits, except *p*-values less than 0.0001, which will be reported as <0.0001. Categorical data will be summarised 2 ways, by subject and by timepoint. Subject data will be summarised using the count of distinct subjects that fall into the category and the percentage of the total number of subjects. Timepoint data will be summarised using the count of the assessments that fall into the category and the percentage of the total number of assessments. Percentages will be rounded up or down to the next integer percentage. Population counts (either number of subjects or number of timepoints at the assessment) for each treatment group will be used as the denominator in the calculation of percentages unless otherwise specified.

#### **8.5.1.2. Baseline**

For all continuous ECG parameters, baseline is defined as the mean of the measured ECG intervals from the 3 ECG timepoints recorded predose (-45, -30, and -15 minutes) on Day 1. For T-wave morphology and U-wave presence, baselines include all categories that occur across all replicates at the 3 predose timepoints on Day 1.

#### **8.5.1.3. Concentration-QTc Analysis (Primary Analysis)**

The relationship between KL1333 plasma concentration and  $\Delta$ QTcF will be quantified using a linear mixed-effects modelling approach with  $\Delta$ QTcF as a dependent variable, drug plasma

concentration as a continuous covariate (ie, 0 for placebo), centred baseline QTcF (ie, baseline QTcF for individual subject at each postbaseline timepoint subtracting the population mean baseline QTcF for all subjects) as an additional covariate, study treatment (active = 1 or placebo = 0) and time (ie, all postbaseline timepoints on Days 1, 2, and 10) as categorical factors, and a random intercept and slope per subject. The degree of freedom estimates will be determined by the Kenward-Roger method. From the model, the slope (ie, the regression parameter for the concentration) and the treatment effect-specific intercept (defined as the difference between active and placebo) will be estimated together with 2-sided 90% CIs. The estimates for the time effects will be reported with degrees of freedom and SE.

The geometric mean of the individual  $C_{\max}$  values for subjects at each dose of active drug will be determined. The predicted effect and its 2-sided 90% CI for  $\Delta\Delta\text{QTcF}$  (ie, slope estimate + treatment effect-specific intercept) at this geometric mean  $C_{\max}$  will be obtained. If the upper bound of the 2-sided 90% CI of the model-predicted QTcF effect is below 10 msec at clinically relevant plasma levels of KL1333, it will be concluded that KL1333 does not cause clinically-concerning QTc prolongation.

The plot of the observed median-quantile KL1333 concentrations and associated mean  $\Delta\Delta\text{QTcF}$  (90% CI) adjusted for diurnal effects together with the regression line presenting the predicted  $\Delta\Delta\text{QTcF}$  will be used to evaluate the adequacy of the model fit to the assumption of linearity and the impact on quantifying the concentration-response relationship. The observed  $\Delta\text{QTcF}$  values from the active groups will be adjusted by the estimated time effect from the concentration-QTc model (ie, the estimated diurnal effect under the placebo treatment). The individually estimated  $\Delta\Delta\text{QTcF}_{ij}$  equals the individual  $\Delta\text{QTcF}_{ij}$  for subject  $i$  administered with KL1333 at timepoint  $j$  minus the estimation of time at timepoint  $j$  (ie, time effect). Additional exploratory analyses (via graphical displays and/or model fitting) will include accounting for a delayed effect (hysteresis) and the justification for the choice of the PD model (linear versus nonlinear) as follows.

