**Number of subjects:**

Part A: 8 healthy subjects (6 active:2 placebo) will be studied in 1 cohort (Group A1). Up to 2 further cohorts of 8 healthy subjects may be included (ie, maximum of 24 healthy subjects total in Part A).

Part B: 8 healthy subjects (6 active:2 placebo) will be studied in each of 2 cohorts (Groups B1 and B2). Up to 3 further cohorts of 8 healthy subjects may be included (ie, maximum of 40 healthy subjects total in Part B).

Part C: 8 patients with mitochondrial disease (6 active:2 placebo) will be studied in 1 dosage group.

Part D: 8 healthy subjects (6 active:2 placebo) will be studied in each of 2 cohorts (Groups D1 and D2).

Total number of subjects in Parts A to D: 48 to 88 subjects.

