#### **8.5.1.3.1. Investigation of Hysteresis**

Hysteresis will be assessed by graphical methods based on the least squares (LS) mean difference of  $\Delta\text{QTcF}$  between KL1333 and placebo ( $\Delta\Delta\text{QTcF}$ ) for each postbaseline timepoint and the mean concentrations of KL1333 at the same timepoints. In addition, hysteresis plots will be given for mean  $\Delta\Delta\text{QTcF}$  and the mean concentrations. If a QT effect ( $\Delta\Delta\text{QTcF}$ ) >10 msec cannot be excluded in the 2 highest dose groups from the by-timepoint analysis and if a delay between peak plasma levels and peak QT effect of more than 1 hour is present, other concentration-QTc models such as a model with an effect compartment may be explored. With the provision stated above, hysteresis will be assumed if the curve shows a counter clockwise loop. A significant treatment effect-specific intercept is not biologically plausible and therefore may also be indicative of hysteresis, if it cannot be explained by a nonlinear relationship.

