#### **8.5.1.4. By-timepoint Analysis**

The analysis for QTcF will be based on a linear mixed-effects model with  $\Delta\text{QTcF}$  as the dependent variable, time (ie, all postbaseline timepoints on Days 1, 2, and 10: categorical), treatment (KL1333 and pooled placebo), and time by treatment interaction as fixed effects, and baseline QTcF as a covariate. An unstructured covariance matrix will be specified for the repeated measures at postbaseline timepoints within subject. If the model with an unstructured covariance matrix fails to converge, another covariance matrix such as compound symmetry and autoregressive will be considered. From this analysis, the LS mean and a 2-sided 90% CI will be calculated for the contrasts “KL1333 – placebo” for each dose and each postbaseline timepoint on Days 1, 2, and 10, separately.

For HR, PR, and QRS the analysis will be based on the change from baseline postdosing ( $\Delta\text{HR}$ ,  $\Delta\text{PR}$ , and  $\Delta\text{QRS}$ ). The same (by-timepoint analysis) model will be used as described for QTcF. The LS mean, SE, and 90% CI from the statistical modelling for both change-from-baseline and the time-matched, placebo-adjusted change-from-baseline values will be listed in the tables and graphically displayed.

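### The concentration-QTc prediction omits the multiplication of the slope by Cmax, and the by-timepoint model has no dose levels for the per-dose contrasts it promises

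*Protocol*

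**What the plan says.** Section 8.5.1.3 fits a linear mixed model to the change from baseline in QTcF, with plasma concentration as a continuous covariate and treatment as an active/placebo factor. It estimates "the slope (ie, the regression parameter for the concentration) and the treatment effect-specific intercept (defined as the difference between active and placebo"). The geometric mean Cmax is found at each dose, and the predicted placebo-corrected effect is then defined as ("ie, slope estimate + treatment effect-specific intercept) at this geometric mean" Cmax. The decision follows: "If the upper bound of the 2-sided 90% CI of the model-predicted QTcF effect is below 10 msec" at clinically relevant plasma levels, the conclusion is that there is no clinically concerning prolongation. The same section describes a plot of observed effects against concentration, "together with the regression line presenting the predicted" effect.

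Section 8.5.1.4 specifies the by-timepoint model with time, "treatment (KL1333 and pooled placebo), and time by treatment interaction as fixed effects", and baseline QTcF as a covariate. It promises KL1333-minus-placebo contrasts "for each dose and each postbaseline timepoint on Days 1, 2, and 10, separately". Section 8.5.1.3.1 uses those results: other models may be explored if an effect above 10 msec "cannot be excluded in the 2 highest dose groups from the by-timepoint analysis" and the peak effect lags the peak concentration by more than 1 hour.

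Section 7.3.5.2 says the continuous ECG data are archived without being extracted or analysed, and that any later analysis is reported outside this study.

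**The concern.** There are two faults of specification.

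First, the predicted effect is the quantity compared with 10 msec. A slope in msec per concentration unit cannot be added to an intercept in msec. The printed sum is the model's prediction at a concentration of 1 unit, so its value depends on whether concentrations are entered in ng/mL or µg/mL, and its confidence interval belongs to that same wrong quantity.

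Second, a treatment factor with two levels and no dose term gives one active-minus-placebo difference per timepoint. The plan promises one per dose, and the later trigger needs the two highest doses separately.

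Section 3.4 says the recordings are collected with a view to supporting a thorough QT study waiver. An error in the decision formula therefore matters if the analysis is ever run from this text.

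**Working it through.** The protocol states no predicted effect, power or sample size for this analysis, so there is no figure of its own to reproduce.

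**1. The prediction.** Write θ for the treatment intercept (msec), β for the concentration slope (msec per unit) and C for the geometric mean Cmax. Time and baseline terms cancel in the active-minus-placebo difference, leaving:

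- model prediction: θ + β × C, with variance Var(θ) + C² Var(β) + 2C Cov(θ, β)
- printed expression: θ + β, with variance Var(θ) + Var(β) + 2 Cov(θ, β), which is the case C = 1.

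Inputs: mean Cmax of total KL1333 at 200 mg is 1385.12 ng/mL (Table 3, Section 1.6). The slope is assumed, since the protocol gives none; θ is set to 0.

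- Slope 0.006 msec per ng/mL: correct 0.006 × 1385.12 = 8.3 msec; printed 0.006 msec.
- Same slope in µg/mL (6 msec per µg/mL): correct 6 × 1.38512 = 8.3 msec; printed 6 msec. Only the printed answer moves with the unit.
- True effect of 20 msec at that Cmax: slope 20 / 1385.12 = 0.0144 msec per ng/mL; printed 0.014 msec, or 14.4 msec in µg/mL.
- The same 20 msec on the free-KL1333 scale (Table 2, 24.68 ng/mL at 200 mg): slope 20 / 24.68 = 0.81; printed 0.81 msec.

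**2. How the 10 msec rule would behave if the text were coded literally.** This is a simplified simulation in ng/mL: random intercept, no random slope, variance components treated as known, 11 timepoints and 1000 runs per scenario. The between-subject SD of 5 msec and within-subject SD of 6 msec are assumptions. Two cohorts means the planned Part B ("8 healthy subjects (6 active:2 placebo) will be studied in each of 2 cohorts (Groups B1 and B2"), 12 active and 4 placebo in total. Five cohorts means 30 and 10. Entries are the percentage of runs in which the upper bound reaches 10 msec.

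| Slope-driven effect at top Cmax | Intercept | 2 cohorts: printed / correct | 5 cohorts: printed / correct |
|---|---|---|---|
| 0 msec | 0 | 12.9 / 11.2 | 0.0 / 0.5 |
| 10 msec | 0 | 11.0 / 94.5 | 0.1 / 91.7 |
| 20 msec | 0 | 12.8 / 100 | 0.2 / 100 |
| 0 msec | 3 msec | 41.3 / 34.1 | 4.9 / 9.0 |
| 20 msec | 3 msec | 42.3 / 100 | 5.0 / 100 |

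Down each printed column, at a fixed intercept, the failure rate hardly changes with the true concentration effect. It does move with the intercept and its precision.

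A cruder noncentral-t approximation shows the same. With SE = SD × √(1/12 + 1/4) = 0.577 × SD and a near-zero intercept, the printed rule fails in about 5%, 34% and 50% of cases for assumed SDs of 5, 8 and 10 msec. At 30:10 the figures are about 0%, 4% and 15%.

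**3. The by-timepoint model.** With two treatment levels, the contrast at each time is one treatment main effect plus one interaction term, so there is one estimate per time. With D doses the plan promises D per time. A pooled contrast averages over doses. As an illustration, take equal cohorts of 6 active subjects and an effect confined to the top dose. The pooled contrast shows 6/12 = one half of that effect with two cohorts and 6/30 = one fifth with five. The trigger's question about the two highest dose groups cannot be answered from it.

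**The case against.** The strongest reply is that the meaning is plain. The sentence asks for the prediction at the geometric mean Cmax. The slope has just been defined as the coefficient of concentration. The decision is taken at clinically relevant plasma levels, and the same section draws the fitted line over concentration. A competent programmer would evaluate the line at Cmax and read the parenthesis as naming its two terms. Likewise, pooled placebo means placebo pooled across cohorts, and the promise of contrasts for each dose shows which treatment levels were meant. This stands: the intent is recoverable in both places, and both are errors of wording.

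It is also fair that nothing this study will report rests on the formula, given Section 7.3.5.2, and that the ECG objective is exploratory (Section 2.1). This limits the impact.

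What the reply does not remove is that the only explicit formula for the decision quantity is wrong, and that the explicit list of model terms contradicts the explicit list of outputs. A specification written ahead of the data should not depend on the analyst repairing it.

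**Conclusion.** Both faults stand as errors in the written specification, of modest consequence. The printed prediction omits a factor of Cmax. In ng/mL it turns 8.3 msec into 0.006 msec under the assumed slope, and if coded literally the rule would be nearly blind to a concentration-driven effect. The by-timepoint model as listed cannot yield the per-dose contrasts or serve the two-highest-doses trigger.

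The algebra needs no assumption. The sizes do: the slope and SDs are assumed, the simulation is simplified, and the Cmax values are arithmetic means from the earlier study, whose total-KL1333 assay may have read low (Section 1.6).

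A reader might infer more than the documents support:

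- **That the 10 msec rule could hardly ever fail, or that a steep slope would be declared safe.** Even coded literally, the rule can fail through the intercept and its standard error, in roughly 5% to 50% of cases at 12:4 over the assumed SDs. The surrounding text also points to evaluation at Cmax.
- **That hysteresis and linearity go unchecked.** The plots in Section 8.5.1.3.1 can use the KL1333-minus-placebo difference at each timepoint, which the model as written supplies. Section 8.5.1.3.2 checks linearity separately with residual plots, LOESS and a quadratic term. Only the trigger for other models is affected.
- **That Group A1's fasted and fed periods collide in the repeated-measures model.** No text says both periods enter one model under the same time labels, and handling of periods is ordinary SAP detail.
- **That the unstructured covariance matrix is unworkable.** Section 8.5.1.4 already provides simpler structures if it does not converge.

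**What to change.** In Section 8.5.1.3, state the predicted placebo-corrected effect as slope estimate × geometric mean Cmax + treatment effect-specific intercept. State that its 2-sided 90% CI comes from the joint covariance of the two estimates, and fix the concentration unit.

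In Section 8.5.1.4, define treatment as a factor with one level per KL1333 dose plus pooled placebo. The promised contrasts and the trigger in Section 8.5.1.3.1 then follow without further change. Carry both corrections into the SAP, or whichever document governs the ECG analysis, before any extraction.

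The cost is wording, plus wider per-dose intervals than a pooled active group would give. With equal SDs and ignoring degrees of freedom, the SE ratio is √(1/6 + 1/4) / √(1/12 + 1/4) = 0.645 / 0.577 = 1.12 for two cohorts, and √(1/6 + 1/10) / √(1/30 + 1/10) = 0.516 / 0.365 = 1.41 for five. The intervals are therefore about 12% and 41% wider. That is the price of the per-dose results the plan already promises.
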